#### Safety analyses

Safety analyses will be performed for patients included in analysis set SAS. Percentage of patients with acute or chronic grade 3 or higher treatment-related toxicity, incidence of AEs, clinical laboratory information, vital signs, ECOG performance status, and weight, will be tabulated and summarized. Incidence of AEs will be summarized overall and with separate summaries for SAEs, AEs leading to discontinuation, AEs leading to death, etc. The overall safety and tolerability will be assessed throughout the study period. All AE data will be listed individually by patient identifier.

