##### Safety Analysis Set (SAS)

All patients who received at least 1 fraction of radiation and for whom any valid post-baseline safety data are available will be included in the safety analysis set. When assessing safety and tolerability, summaries will be produced based on the safety analysis set. Patients are analyzed according to the actual treatment received.

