##### Secondary endpoints

Measurement of grade 3 or higher treatment-related toxicity during or within 24 months after completion of PULSAR, according to the CTCAE v5.0.Disease progression free survival (PFS), defined as the time from enrollment to the first objectively documented disease progression, either in or out of the treated field per radiographic and/or clinical evaluation, or death due to any cause. Participants who experience death or are lost to follow-up prior to 1 year will be assessed by their last radiographic/clinical evaluation.Overall survival (OS), defined as the time between enrollment and death of any cause. Participants who are lost to follow-up prior to 1 year will be censored at the date of their last documentation in the medical record system.Impact of PULSAR on symptoms/quality of life as measured by the UW-QoL and FACT-H&N validated questionnaires.Measurement of the frequency of re-simulation and/or adaptive planning required with PULSAR.Evaluation of the standard of care tumor and OAR dosimetry with PULSAR.Evaluation of the safety and efficacy of combination PULSAR and cancer-directed systemic therapy in enrolled patients receiving cancer-directed systemic therapy will be descriptive and exploratory.

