##### Efficacy analyses

Primary endpoint: Primary endpoint analyses will be performed on patients included in analysis sets FAS and EAS across the whole cohort, as well as separate analyses stratifying patients by Human Papillomavirus/p16 status and receipt of cancer-directed systemic therapy, both in general and by agent type (chemotherapy, targeted, immunotherapy). For the primary endpoint, we will calculate the percentage and construct 95% exact confidence interval for local control rate. Additionally, Kaplan–Meier method and cumulative incidence functions considering distant progression or death as a competing risk will be used to provide estimates of the local control at 1-year, median local control, and cumulative incidence of local control at 1-year, with corresponding 95% confidence intervals.Secondary Endpoints: Secondary endpoint analyses will be performed on patients included in analysis sets FAS and EAS across the whole cohort, as well as separate analyses stratifying patients by Human Papillomavirus/p16 status. For the secondary endpoints of PFS and OS, Kaplan–Meier method and cumulative incidence curves treating death as a competing risk will be used to provide estimates of the PFS/OS at 1-year, median PFS/OS, and cumulative incidence of PFS/OS at 1-year. Corresponding 95% confidence intervals will also be presented.

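### The 24-month grade 3+ toxicity endpoint is summarised as a crude percentage of the safety set, so patients lost before 24 months count as event-free and the figure is biased modestly downward

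*Protocol article*

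**What the plan says.** Four parts of the protocol article bear on this point.

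- **Secondary endpoints.** The first secondary endpoint is "Measurement of grade 3 or higher treatment-related toxicity during or within 24 months after completion of PULSAR, according to the CTCAE v5.0".
- **Safety analyses.** The set is fixed: "Safety analyses will be performed for patients included in analysis set SAS". So is the summary: "Percentage of patients with acute or chronic grade 3 or higher treatment-related toxicity, incidence of AEs", to be tabulated.
- **Safety Analysis Set (SAS).** The set comprises "All patients who received at least 1 fraction of radiation and for whom any valid post-baseline safety data are available". It sets no minimum follow-up.
- **Patient follow-up.** After the last fraction, toxicity is measured at visits at 3, 6, 12, 18 and 24 months, each within 28 days.

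Methods that allow for incomplete follow-up are named elsewhere. For local control, Efficacy analyses states "Kaplan–Meier method and cumulative incidence functions considering distant progression or death as a competing risk will be used". It continues: "For the secondary endpoints of PFS and OS, Kaplan–Meier method and cumulative incidence curves treating death as a competing risk will be used". Study endpoints also says how early death or loss is treated for local control and PFS, and how loss is treated for OS. Toxicity has neither a method nor a rule of this kind.

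**The concern.** A percentage over the whole SAS treats every patient without a recorded event as observed and event-free for the entire window. The article does not say so in words, but it follows from the chosen numerator and denominator. A patient with one toxicity assessment who is lost two months after treatment adds nothing to the numerator and a full unit to the denominator of a 24-month figure.

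Incomplete follow-up is likely here. Study population admits patients with metastatic disease, comorbidities and poor performance status, and Sample size determination itself allows for drop-out. The error runs in the favourable direction. Safety is Secondary Aim 1, and the Discussion says PULSAR may replace existing palliative regimens if its safety and efficacy are confirmed. A reader comparing its late toxicity with that of another regimen could be misled by a figure that does not show how many patients were still under observation.

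**Working it through.** **Plan's own figure.** The article states no expected rate for this endpoint, so there is none to reproduce. The sample size concerns local control only: 38 patients, 85% against 65%, two-sided exact test. It reproduces, with rejection at 31 or more controlled and power 0.799. It does not depend on the toxicity summary.

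**Inputs, all assumed unless stated.** Time t is in months after treatment.
- Window to 24 months: from Secondary endpoints.
- Late grade 3+ toxicity: constant hazard from month 3 to month 24, giving 20% if nobody died or was lost (net risk). h_t = -ln(0.8)/21 = 0.01063 per month.
- Death: exponential, median m = 6, 9, 12, 18 or 24 months. h_d = ln(2)/m.
- Loss: exponential, independent of toxicity, 10% or 20% a year. h_c = -ln(0.9)/12 = 0.00878 or -ln(0.8)/12 = 0.01860.

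**Formula.** The expected proportion with an event observed by month 24 is

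I(c) = exp[-3(h_d + c)] × h_t/(h_t + h_d + c) × {1 - exp[-21(h_t + h_d + c)]}

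The crude percentage is I(h_c). The cumulative incidence with death competing and losses censored estimates I(0).

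**Worked case, median survival 12 months, 10% yearly loss.** h_d = 0.05776.
- Cumulative incidence: 0.8409 × 0.01063/0.06839 × 0.7622 = 9.96%.
- Crude: 0.8190 × 0.01063/0.07717 × 0.8022 = 9.05%.
- Gap: 0.91 points, or 9.1% of the cumulative incidence.

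**Full range.**

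| Median OS (months) | Cumulative incidence | Crude, 10% loss | Gap (relative) | Crude, 20% loss | Gap (relative) |
|---|---|---|---|---|---|
| 6 | 5.5% | 5.1% | 0.4 points (8%) | 4.7% | 0.9 points (16%) |
| 9 | 8.1% | 7.4% | 0.7 (9%) | 6.7% | 1.4 (17%) |
| 12 | 10.0% | 9.1% | 0.9 (9%) | 8.2% | 1.8 (18%) |
| 18 | 12.4% | 11.2% | 1.2 (10%) | 10.0% | 2.4 (19%) |
| 24 | 13.9% | 12.5% | 1.4 (10%) | 11.2% | 2.7 (20%) |

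**Death alone.** With h_c = 0 the crude percentage is I(0), identical to the cumulative incidence in every row. Only loss or incomplete follow-up opens a gap.

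**Dependence on survival.** Both measures move from 5.5% to 13.9% as median survival goes from 6 to 24 months, with the toxicity hazard unchanged. The fraction alive and followed at month 24, exp[-24(h_d + h_c)] when toxicity does not end follow-up, is 5% to 41% at 10% loss. A bare percentage shows none of this.

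**Sensitivity.** With toxicity arising from month 0, one-year survival of 30%, 50% or 70%, and the same 20% net risk, the gap is 0.5 to 2.4 points across 10-20% yearly loss. With 5% net risk in the month 3-24 model and 10% loss, it is 0.1 to 0.35 points.

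**The case against.** Several points on the other side stand.

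- **The bias is small beside sampling error.** At 10% loss it is 0.2 to 0.6 of a patient among 43 (43 × 0.0043 to 43 × 0.0138). The exact 95% CI for 4/43 is 2.6% to 22.1%.
- **No decision depends on it.** The formal safety rule covers the first 15 patients and a three-month window. The 24-month endpoint has no threshold or test, and General calls all analyses descriptive.
- **Capture is wider than clinic visits.** The trial calendar allows some assessments by telemedicine, SAEs are monitored continuously, and related events remain reportable beyond six months. This lowers the effective loss rate.
- **The loss rates are assumptions.** A reader might take the step from 38 to 43 patients (5/43 = 11.6%) as support for 10% a year. It is not a yearly rate, it includes patients who become ineligible, and anyone who leaves before a first fraction never enters the SAS.

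A reader might also infer that efficacy is adjusted for follow-up while toxicity is not. The article does not support that contrast in full: the primary local control figure is itself a percentage with an exact interval, and the time-to-event estimates are additional to it.

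The objection that this is detail left to an analysis plan carries less weight. A percentage in the safety set is conventional, and an unseen plan may add more, but the article itself chooses both the measure and the denominator.

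**Conclusion.** The point holds for loss and incomplete follow-up. The stated summary is biased downward by about 0.4 to 1.4 points at 10% yearly loss and 0.9 to 2.7 points at 20%. These sizes rest on 20% net late toxicity, median survival of 6 to 24 months, constant hazards and loss unrelated to toxicity. The direction needs only that some event-free patients leave follow-up while still at risk.

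Two stronger readings are tempting. The first is that deaths also make the percentage too low. They do not: death is a competing event, and with complete follow-up the crude percentage is a valid absolute risk. The second is to set the crude 5.1-12.5% against the 20% net risk and call the shortfall bias. That 20% describes patients who neither die nor are lost, and a competing-risk analysis would not report it either. Survival matters for interpretation, which is why numbers at risk are needed.

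This is a modest, inexpensive improvement to a secondary descriptive endpoint. It does not threaten the trial's conclusions.

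**What to change.** In Safety analyses, keep the crude percentage as a descriptive line. As the summary of the endpoint, report the cumulative incidence of first grade 3 or higher treatment-related toxicity from the first fraction to 24 months after the last fraction. Treat death as a competing event and censor patients who are lost at their last toxicity assessment. Give a 95% CI and the numbers at risk at 3, 6, 12, 18 and 24 months.

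The cost is some wording and one more table or curve from data already collected. The reported figure will be slightly higher and the late intervals wider. Censoring assumes that lost patients have the same later risk as those still followed, and the report should say so. The sample size and the 15-patient, three-month stopping rule do not change.

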#### Symptom/quality of life analyses

Analysis of data related to the symptom/quality of life impact of PULSAR using the UW-QoL and FACT-H&N validated questionnaires will be primarily descriptive and exploratory.

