In this context, PULSAR is an appealing option for patients requiring palliative radiation therapy for HNC. Given the potential efficacy, safety, symptomatic, and logistical benefits of this radiation regimen, we hypothesize that PULSAR delivered with HyperArc© technology will result in improved local control and similar or improved symptom relief while mitigating toxicity risk compared with existing palliative radiation regimens in patients with de novo or recurrent HNC who are not candidates for standard of care definitive treatment(s), including standard of care SBRT. To test this hypothesis, we will conduct a prospective clinical trial of PULSAR in this patient population. Because PULSAR is a newer technique, it has not yet been comprehensively studied, particularly in combination with HyperArc© technology. To our knowledge, there are currently nine early phase clinical trials prospectively evaluating PULSAR in some capacity (NCT 04677413, 04779489, 04786093, 04889066, 05021237, 05846646, 05846659, 06044857, 06359275), none of which are in HNC. Thus, validation of its safety and feasibility is first required prior to larger-scale prospective studies of efficacy in HNC. Herein, we propose an early safety and feasibility study of palliative PULSAR delivered with HyperArc© technology in patients with de novo or recurrent, localized or metastatic HNC who are ineligible for or decline standard of care definitive treatment(s).

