#### Patient follow-up

Symptomatic response will be assessed through subjective patient report and completion of the UW-QoL and FACT-H&N questionnaires (Supplemental Material). Treatment-related toxicity during and after completion of PULSAR will be measured according to the CTCAE v5.0. Local tumor response will be assessed clinically and/or radiographically (e.g., by CT, PET, MRI), as applicable. Patient follow-up will be measured starting from the time of trial enrollment. Patient clinical assessments during PULSAR will occur within 7 days of each radiation treatment and consist of brief history, physical exam, and assessment of treatment-related toxicity. After receipt of the last PULSAR fraction, patients will be assessed clinically at 3 months +/- 28 days, 6 months +/- 28 days, 12 months +/- 28 days, 18 months +/- 28 days, and 24 months +/- 28 days post-treatment. These follow-up visits will consist of a history and physical exam, completion of the UW-QoL and FACT-H&N questionnaires, and measurement of toxicity. Surveillance imaging will be obtained per standard of care. Patients who experience disease progression will receive standard of care treatment(s) at the discretion of the treating physician. Patient enrollment, treatment, and follow-up is shown in Fig. 2.

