### Statistical methods and considerations

#### General

All analyses will be descriptive and will be presented by treatment period and overall as appropriate. Data collected in this study will be presented using summary tables and patient data listings. Continuous variables will be summarized using descriptive statistics, specifically the mean, median, standard deviation, minimum, and maximum. Categorical variables will be summarized by frequencies and percentages.

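### The symptom and quality-of-life scores have a descriptive summary but no handling of death or missing forms, so plain visit-by-visit means could rise through loss of the sickest patients alone

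*Protocol article*

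**What the plan says.** All references are to the protocol article.

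- **Status of the endpoint.** Symptomatic impact is Secondary Aim 3. The Secondary endpoints section lists it as "Impact of PULSAR on symptoms/quality of life as measured by the UW-QoL and FACT-H&N validated questionnaires". The Background hypothesis includes it too: PULSAR with HyperArc "will result in improved local control and similar or improved symptom relief while mitigating toxicity risk compared with existing palliative radiation regimens".
- **Collection.** Both questionnaires are completed before treatment (Pretreatment evaluations) and again after it. Patient follow-up states: "These follow-up visits will consist of a history and physical exam, completion of the UW-QoL and FACT-H&N questionnaires, and measurement of toxicity". The visits fall at 3, 6 and 12 months after the last fraction, then "18 months +/- 28 days, and 24 months +/- 28 days post-treatment".
- **Analysis.** The section Symptom/quality of life analyses is one sentence, which says that analysis of data from the "UW-QoL and FACT-H&N validated questionnaires will be primarily descriptive and exploratory". The General paragraph of the statistical section adds "All analyses will be descriptive and will be presented by treatment period and overall as appropriate" and "Continuous variables will be summarized using descriptive statistics, specifically the mean, median, standard deviation, minimum, and maximum".
- **Death and loss.** Under Primary endpoint and Secondary endpoints, local control and PFS use the last evaluation for patients who die or are lost before one year, and OS censors patients who are lost. Nothing equivalent is given for the questionnaires.

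**The concern.** The cohort is palliative. The Study population section admits patients with metastatic disease, comorbidity or poor performance status. The Background says that local progression worsens symptoms and that locoregional progression is a frequent cause of death in this disease. On the protocol's own account, then, bad symptoms and leaving observation are linked.

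A descriptive mean at 12 or 24 months describes the patients who are alive and well enough to fill in a form. The baseline mean describes nearly everyone. If those who leave had the worse scores, the later mean is higher even when every individual score is unchanged. The median is open to the same selection, so printing it beside the mean does not help.

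What is at stake is how a stated secondary aim is read. With a single arm, no control group would show the same drift, and a rise in the mean could be taken for symptom relief.

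**Working it through.** **Plan's own figure.** There is none for this endpoint. The sample size calculation concerns only one-year local control, and this point does not depend on it.

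**Step 1: does the text settle who is in the later summaries?** Efficacy analyses assigns the secondary endpoints to the full analysis set (FAS) and the evaluable set. An analysis set defines who is counted; it does not create scores. A patient who has died has no questionnaire. With no imputation or death rule stated, a summary of raw scores on the FAS reduces in practice to the forms available. The Fig. 2 footnote allows completion by telephone or electronically, which can reduce non-response from illness but not loss through death.

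**Step 2: how large could the shift be?** The documents give neither a completion rate nor a link between score and response, so the inputs are assumptions:

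- a higher score is better, scores are roughly normal, and no patient's score changes;
- a fraction f of patients answers at a given visit (0.6, 0.5 or 0.4);
- the score correlates r with a latent tendency to be still answering (0.3 to 0.5), and those above a cut-off on that tendency answer.

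The mean among those answering then exceeds the all-patient mean, in SD units, by

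shift = r × φ(z) / f,

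where z is the standard normal cut-off leaving a fraction f above it and φ is the standard normal density.

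| f answering | φ(z) | φ(z)/f | r = 0 | r = 0.3 | r = 0.5 |
|---|---|---|---|---|---|
| 0.6 | 0.386 | 0.644 | 0 | 0.19 | 0.32 |
| 0.5 | 0.399 | 0.798 | 0 | 0.24 | 0.40 |
| 0.4 | 0.386 | 0.966 | 0 | 0.29 | 0.48 |

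A simulation at f = 0.6 and 0.5 agrees with the formula (0.193 and 0.321; 0.239 and 0.399).

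**Step 3: how far does this depend on the inputs?** With 80% answering, the shift at r = 0.3 is 0.10 SD. With 50% answering and r = 0.7 it is 0.56 SD. At r = 0 it vanishes at any completion rate. Real decline in the patients who remain would pull the observed mean back down, so the observed mean need not rise.

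**Step 4: does paired change remove it?** In this no-change setting, each respondent's change from baseline is zero, so the mean change is zero whatever f and r are. The respondents' own baseline mean would show the selection directly, because it would sit above the baseline mean of the full cohort by the shift in the table.

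**The case against.** The strongest case against the point has four parts.

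1. **A respondents-only mean is not written down.** A reader might infer that the plan commits to nothing but means of whoever answers. The text does not support that. It says primarily descriptive, which leaves room for more; the General paragraph also names other statistics and listings by patient; and secondary endpoints are assigned to the FAS and evaluable set. Change from baseline is itself a continuous variable and could be summarised under the same paragraph. This stands: the bias belongs to one reading of the plan, although the most literal one.
2. **This is analysis-plan detail.** The article condenses a fuller protocol, and a statistical analysis plan may exist. Handling of missing forms is often left there. This stands in part. However, the article itself names the summary statistics and gives death or loss rules for the endpoints around this one, and an analysis plan could comply with it and stop there.
3. **The size is assumed.** This stands in full. No document gives completion, survival or correlation figures, and the shift can be zero. Any statement that the scores will rise goes beyond the documents.
4. **Little turns on it.** The analysis is labelled exploratory, with no test or threshold, and deaths are reported through OS and PFS. This stands as to the trial's decisions. It does not remove selection from a published mean, and an OS curve does not tell the reader who contributed to each questionnaire mean.

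**Conclusion.** The point holds in conditional form. The article describes the two questionnaires primarily by simple summary statistics and, unlike local control, PFS and OS, gives no handling of death or missing forms. If this is applied as plain visit-by-visit summaries, later means can rise through selection alone. The size is about 0.2-0.5 SD under the assumptions of 40-60% answering, a correlation of 0.3-0.5 and no true change. It is zero if missingness is unrelated to health, and true decline could mask it.

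A reader might go further and conclude that the trial's symptom result is bound to be biased toward benefit, or that its conclusion on efficacy is compromised. Neither follows. The first depends on an implementation that the text does not prescribe and on dropout that the documents do not quantify. The second fails because the questionnaires enter no decision rule; the powered question is one-year local control. This is a cheap improvement to a stated secondary summary.

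**What to change.** Add to Symptom/quality of life analyses, before outcome data are examined:

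1. Summarise within-patient change from baseline at each visit, and show beside it the baseline mean of the same respondents.
2. For the whole FAS, tabulate at each visit the numbers who completed the form, died and were not assessed. If any proportion improved is reported, deaths are never counted as improved.

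A mixed model for repeated measures is optional support only. It relies on a missing-at-random assumption and does not resolve truncation by death, since it implicitly continues score trajectories past the date of death.

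The cost is a few lines of text and a few extra tables from data already collected. The downside is that the apparent symptom benefit may be smaller. Sample size, the primary analysis and the safety stopping rule are unchanged.
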